## Abstract

**Background:**

The United States continues to experience an alarming rise in opioid use that includes women who become pregnant and related neonatal abstinence syndrome (NAS) in newborns. Most newborns experiencing NAS require nonpharmacological care, which entails, most importantly, maternal involvement with the newborn. To facilitate positive maternal-newborn interactions, mothers need to learn effective caregiving NAS strategies when they are pregnant; however, an enormous gap exists in the early education of mothers on the symptoms and progression of NAS, partly because no education, training, or other interventions exist to prepare future mothers for the challenges of caring for their newborns at risk for NAS.

**Objective:**

In this paper, we describe a mixed methods, multistage study to adapt an existing mobile NAS tool for high-risk pregnant women and assess its usability, acceptability, and feasibility in a small randomized controlled trial.

**Methods:**

Stage 1 will include 20 semistructured interviews with a panel of neonatology experts, NAS care providers, and mothers with experience caring for NAS-affected newborns to gather their recommendations on the management of NAS and explore their perspectives on the care of these newborns. The findings will guide the adaptation of existing mobile NAS tools for high-risk pregnant women. In stage 2, we will test the usability, acceptability, and feasibility of the adapted mobile tool via surveys with 10 pregnant women receiving opioid agonist therapy (OAT). Finally, in stage 3, we will randomize 30 high-risk pregnant women receiving OAT to either receive the adapted mobile NAS caregiving tool or usual care. We will compare these women on primary outcomes—maternal drug relapse and OAT continuation—and secondary outcomes—maternal-newborn bonding; length of newborn hospital stays; readmission rates; breastfeeding initiation and duration; and postpartum depression and anxiety at 4, 8, and 12 weeks postpartum.

**Results:**

This project was funded in July 2020 and approved by the institutional review board in April 2020. Data collection for stage 1 began in December 2020, and as of January 2021, we completed 18 semistructured interviews (10 with NAS providers and 8 with perinatal women receiving OAT). Common themes from all interviews will be analyzed in spring 2021 to inform the adaptation of the NAS caregiving tool. The results from stage 1 are expected to be published in summer 2021. Stage 2 data collection will commence in fall 2021.

**Conclusions:**

The findings of this study have the potential to improve NAS care and maternal-newborn outcomes and lead to commercialized product development. If effective, our new tool will be well suited to tailoring for other high-risk perinatal women with substance use disorders.

**Trial Registration:**

ClinicalTrials.gov NCT04783558; https://clinicaltrials.gov/ct2/show/NCT04783558

**International Registered Report Identifier (IRRID):**

DERR1-10.2196/27382

## Introduction

### Background

The United States is experiencing an alarming rise in opioid use during pregnancy, diagnosis of opioid use disorder (OUD) in pregnancy, and related neonatal abstinence syndrome (NAS) in newborns [1,2]. The percentage of pregnant women reporting opioid misuse increased from 2% to 28% in the United States from 2000 to 2014, and the proportion of pregnant women who entered substance use treatment and reported prescription opioids as their primary substance increased from 16.9% in 1996 to 41.6% in 2014 [3]. NAS is a spectrum of symptoms or signals of substance withdrawal in newborns whose mothers used illicit opioids or were being treated with opioid agonist therapy (OAT; ie, methadone or buprenorphine) during pregnancy [4,5]. NAS rates have dramatically increased from approximately 1.5 to 8.0 per 1000 hospital births from 2004 to 2014 [5-8], which translates to one infant experiencing opioid withdrawal every 15 minutes in the United States [1]. There is evidence that this rate continues to increase as the US Pediatric Health Information System reported an incidence of 20 per 1000 live births in 2016 [9]. NAS signs include tremors, increased irritability, fever, sweating, extreme weight loss, excessive sucking, and inability to sleep [4,10,11]. NAS is an enormously costly public health issue, costing the United States US $563 million in an aggregate associated hospital charge in 2014, largely because of costs associated with lengthy hospital stays, neonatal intensive care unit (NICU) admissions, and higher risk of hospital readmission, and other costly, downstream health costs associated with depression, anxiety, and other difficulties that mothers encounter [1,6,12,13].

Mothers are often unprepared for what they are about to experience before having a baby while using either illicit or licit opioids. Treatment of NAS in the postpartum period is critical in shaping both maternal and newborn outcomes. At least half [14] of the newborns experiencing NAS require nonpharmacological care, which is best delivered by the newborn’s mother or close caregiver [4,15-17]. Up to 95% of NICUs offer some form of nonpharmacological intervention, and it is advised that all infants with in utero exposure to opioids be administered nonpharmacological treatment [14]. Evidence-based, nonpharmacological care for NAS includes rooming together with the mother postdelivery and modification of the environment to support maternal-newborn attachment that promotes a soothing environment for the infant. Specific actions include low-stimulating environments (reduced noise and light), frequent and small feedings, swaddling, promotion of breastfeeding, and continual contact and soothing from the caregiver [15,17-20]. These are all doable now by mothers and other health care providers; however, the missing link is having ready access to an educational platform to promote these strategies, which is precisely what this study is designed to do.

Facilitating successful postpartum maternal-newborn involvement is critical in lowering NICU admissions and hospital readmissions, boosting breastfeeding, shortening hospital stays, decreasing the need for pharmacological intervention for the newborn, reducing the risk of maternal OAT discontinuation, and facilitating maternal-child bonding [13,15,21-24]. However, the challenging NAS signs can hinder maternal-newborn bonding, particularly for women who have substance use disorders (SUDs) who may have difficulty responding to newborns’ cues [15]. To maximize positive maternal-newborn interactions, mothers need to learn effective NAS caregiving strategies when they are pregnant to optimize their preparedness; however, little to no preparedness strategies exist for at-risk pregnant women.

The *American College of Obstetricians and Gynecologists’ Alliance for Innovation on Maternal Health Program* recently developed a maternal safety bundle on obstetric care of women with OUDs, which emphasizes the need to provide caregivers education regarding NAS and newborn care [19]. However, pregnant women in OAT currently receive virtually zero education or consultation for what to expect when they give birth to a baby who is at risk of experiencing NAS. One such education strategy would incorporate caregiving skills based on the promising and recently established Eat, Sleep, and Console (ESC) model that stresses newborn sleep, feeding, and a low-stimulating environment [20]. We previously developed and implemented a mobile instructional tool designed to streamline the assessment of NAS for providers in the NICU. This interactive tool includes evidence-based education modules covering topics such as NAS epidemiology, symptoms, nonpharmacological treatment, and transition to follow-up care [25].

### Objectives

As the long-term caregivers of newborns experiencing NAS, mothers are essential to the successful, nonpharmacological treatment of NAS-affected babies. By adapting our instructional NAS tool, we can address this critical gap and potentially improve outcomes for NAS-affected newborns and their mothers. This study describes a mixed methods, multi-stage study (see Figure 1 for study stage and timeline) to adapt an existing mobile NAS tool for high-risk pregnant women and assess its usability, acceptability, and feasibility in a small randomized controlled trial.

**Figure 1 figure1:**
[figure not shown]
Stage process and time line of study. NAS: neonatal abstinence syndrome; OAT: opioid agonist therapy.

## Methods

### Overview

This study will be carried out in 3 stages. In stage 1, we will conduct semistructured interviews with a panel of NAS care experts and mothers with NAS-affected newborns until saturation is reached (expected n=20) to document their perspectives and gather their recommendations on the care of newborns with NAS. Although findings from stage 1 will ultimately guide the adaptation of the existing mobile NAS tool for high-risk pregnant women, the skills training in the adapted tool will be largely based on elements of ESC. In stage 2, we will test the usability, acceptability, and feasibility of the adapted mobile tool via surveys with 10 pregnant women receiving OAT at 2 facilities in Washington: one that provides methadone as its pharmacotherapy and another that primarily treats patients receiving buprenorphine as their pharmacotherapy. In stage 3, we will randomize 30 high-risk pregnant women seen at these facilities to either receive the adapted mobile NAS instructional tool or usual care. We will compare these participants on numerous maternal and newborn health outcomes at 4, 8, and 12 weeks postpartum, including *primary outcomes*—maternal OAT continuation and maternal drug relapse—and *secondary outcomes*—length of newborn hospital stay, readmission rates, maternal-newborn bonding, breastfeeding initiation and duration, birth satisfaction, and postpartum depression and anxiety.

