**Stage 3:** **Clinical trial comparing NAS tool with usual care**					
	Demographic characteristics	Randomized clinical trial		Demographics and baseline characteristics, such as age, education, marital status, time in the OAT^d^ program, number and age of living children, employment, and ASI-Lite^e^, will be collected at the start of the study to describe the sample and to serve as control variables when comparing groups on the outcomes.	
	Maternal drug use and relapse	Randomized clinical trial		Maternal drug use and relapse will be assessed via ASI-Lite, a standardized semistructured clinical interview that offers clinical information and assesses severity profiles in the following domains: medical, employment, alcohol, drug, psychological, legal, and family and social [34]. It has been shown to have adequate to good internal consistency, good test-retest reliability, independence across the domain composite scores, and agreement with the longer version of the ASI-Lite [34].	
	OAT continuation	Randomized clinical trial		OAT continuation will be assessed via a single question (“Are you currently receiving OAT (Yes or No)? Please explain”).	
	Length of newborn hospital stay and readmission	Randomized clinical trial		These will be determined by single questions: length of newborn hospital stay (“how many days did your newborn stay in the hospital”) and newborn hospital readmission (“has your newborn been readmitted to the hospital for any reason after discharge? If yes, how many times? Please list reasons for each readmission”).	

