### Stage 3: Clinical Trial to Test the NAS Instructional Tool Versus Usual Care to Potentially Improve Postpartum Maternal-Newborn Health Outcomes

#### Data Collection and Inclusion Criteria

Similar to previous stages, we will recruit 30 pregnant women in their third trimester from the same 2 treatment centers to participate in stage 3 of the study. After a brief phone screening, eligible participants will then be consented and randomized 1:1 into either the intervention condition (ie, adapted NAS tool intervention, as given in the *Study Intervention* section) or the control condition (ie, treatment as usual [TAU], as given in the *Study Intervention* section). Participants will be asked to provide demographic and baseline information at this point. Women in the intervention condition will go through the mobile-based NAS instructional tool at least once during pregnancy, with their choice of going through the modules gradually while waiting at the OAT clinic to receive their dose or by scheduling a time to review the modules with research staff outside of the clinic (either at university offices or via a video conference). Participants will be met with a research assistant who will provide them with an iPad and access to the modules (via a private YouTube link), and the research assistant will be available for any questions throughout the review. Participants will be able to create a YouTube account on the iPad and will be able to access, skip, pause, and continue the modules at any time during the duration of the study through the 12-week follow-up period (ie, access after giving birth as well). They will also be able to post questions or comments under private YouTube videos for research staff to see and address. Each participant will also be scheduled for the 3 follow-up appointments (at 4, 8, and 12 weeks postpartum). Follow-up appointments will consist of filling out surveys (Table 1). Participants will be able to complete the survey on their phones or iPads. For completing all study appointments, participants will receive a total of US $125 in Amazon e-gift cards (US $25 after providing demographic and baseline information, US $25 after reviewing the modules with a research assistant, and an additional US $25 Amazon gift card for each of the 3 follow-ups). The inclusion criteria are as follows: (1) a pregnant woman currently undergoing OAT treatment for OUD, (2) age >18 years, and (3) ability to speak and understand English. Exclusion criteria are as follows: recurring (eg, daily or almost daily) thoughts of harming themselves or others in the past 2 weeks.

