#### Adapted NAS Tool Intervention

Pregnant women in this condition will receive the adapted mobile-based NAS instructional tool and TAU. Women in this condition will go through the NAS instructional tool at least once during pregnancy, with their choice of going through the modules gradually while waiting at the OAT clinic to receive their dose or by scheduling a time to review the modules. Participants will have free web access to the tool throughout their third trimester and through 12 weeks postpartum so they can access the modules at any time and as many times as desired, including after giving birth. Women will be randomized 1:1 to the intervention or TAU conditions.

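### Stage 3 draws 30 women from two facilities that differ by OAT drug, so allocation should be stratified by facility and facility named in the GEE: a cheap improvement, not an error

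*Protocol article*

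**What the plan says.** The Overview describes the two recruiting facilities as "one that provides methadone as its pharmacotherapy and another that primarily treats patients receiving buprenorphine as their pharmacotherapy". It then says "In stage 3, we will randomize 30 high-risk pregnant women seen at these facilities". The Background defines the treatment as "opioid agonist therapy (OAT; ie, methadone or buprenorphine) during pregnancy", and the stage 3 eligibility criterion is "a pregnant woman currently undergoing OAT treatment for OUD", with no restriction by drug.

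Allocation is described in two places. Under stage 3, Data Collection and Inclusion Criteria: "eligible participants will then be consented and randomized 1:1 into either the intervention condition". Under Adapted NAS Tool Intervention: "Women will be randomized 1:1 to the intervention or TAU conditions". Both give the ratio and nothing about strata or blocks.

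Table 2 gives examples of demographic and baseline characteristics: "age, education, marital status, time in the OAT" program, children, employment and ASI-Lite. Their stated purpose is "to serve as control variables when comparing groups on the outcomes". Table 1 lists the same items for baseline and adds the Maternal Antenatal Attachment Scale. The stage 3 Data Analysis section tests baseline characteristics across arms, then fits GEE models that adjust for baseline demographic differences, other baseline variables and time. None of these places names facility or OAT drug.

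**The concern.** The facility delivers the treatment whose continuation is a primary outcome, and by the article's own account the two facilities differ in drug. Facility is therefore a natural candidate for a prognostic grouping that is known before randomization.

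With 15 women per arm, chance can easily leave one arm with more women from one facility. If continuation or relapse differs by facility, part of the observed difference between arms would then reflect facility mix. The Strengths and Limitations section says the trial should yield efficacy data to inform a fully powered trial, so a distorted estimate could carry into that planning.

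**Working it through.** The article gives N = 30 and 1:1 allocation. It gives no facility split, no continuation rate by facility or drug, and no power calculation, so there is no stated figure to reproduce. Everything below beyond N and the ratio is an assumption.

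**Step 1. Chance of imbalance.** Assume exactly 15 women per arm, with allocation ignoring facility. If K of the 30 women come from facility A, the number k in the tool arm is hypergeometric: P(k) = C(15, k) × C(15, K − k) / C(30, K).

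- K = 15, split 10 v 5 or worse: 2 × (3003² + 1365² + 455² + 105² + 15² + 1²) / 155,117,520 = 22,199,020 / 155,117,520 = 0.143.
- K = 15, split 9 v 6 or worse: (22,199,020 + 2 × 5005²) / 155,117,520 = 0.466.
- K = 20, split 12 v 8 or worse: 2 × (455 × 6435 + 105 × 6435 + 15 × 5005 + 3003) / 30,045,015 = 0.245.

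**Step 2. What a null tool would show at 10 v 5.** The tool arm has 10 women from A and 5 from B; the control arm has 5 and 10.

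- No facility gap: both arms have the same expected rate, OR 1.0.
- 85% at A, 70% at B: tool (8.5 + 3.5)/15 = 80.0%; control (4.25 + 7)/15 = 75.0%; OR = (12/3)/(11.25/3.75) = 1.33.
- 90% at A, 65% at B: tool (9 + 3.25)/15 = 81.7%; control (4.5 + 6.5)/15 = 73.3%; OR = (12.25/2.75)/(11/4) = 1.62.

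The mirror split is equally likely and gives 1/1.33 = 0.75 and 1/1.62 = 0.62. At the commoner 9 v 6 split the same rates give smaller distortions:

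- 85% and 70%: (11.85/3.15)/(11.4/3.6) = 1.19.
- 90% and 65%: (12/3)/(11.25/3.75) = 1.33.

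**Step 3. Size against sampling error.** For the OR of 1.62, the standard error of the log odds ratio is √(1/12.25 + 1/2.75 + 1/11 + 1/4) = 0.89. The 95% interval is exp(0.482 ± 1.96 × 0.89), about 0.29 to 9.2.

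**Step 4. False-positive rate with no tool effect.** This used 200,000 simulated trials per row, 15 women per facility and per arm, one time point and a two-sided 5% level. A two-proportion z test that ignores facility is compared with a Mantel-Haenszel test stratified by facility. It is a simplified stand-in for the planned GEE.

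| Assumed continuation | z test, all trials | z test, 10 v 5 or worse | Stratified, all trials | Stratified, 10 v 5 or worse |
|---|---|---|---|---|
| 80% and 80% | 4.9% | 4.7% | 4.5% | 4.6% |
| 80% and 70% | 5.4% | 5.8% | 4.7% | 4.9% |
| 80% and 60% | 5.5% | 7.3% | 4.6% | 4.8% |
| 90% and 60% | 5.5% | 9.6% | 4.8% | 4.6% |
| 90% and 50% | 5.6% | 12.4% | 4.9% | 4.7% |

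Averaged over all allocations, ignoring facility does little to the error rate. Given a marked imbalance it raises the rate when the facilities differ, and stratified analysis removes that rise.

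**The case against.** The strongest objection is that this is a condensed article. A 1:1 ratio is compatible with stratified, blocked lists, and such detail often sits in a full protocol or analysis plan that is not shown. That stands: a reader might infer that allocation is unstratified, but the article does not say so.

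A reader might also infer that the planned model cannot correct a facility imbalance. The documents do not support that. Table 2 introduces its control variables as examples, nothing in the Data Analysis section excludes facility, and each woman's facility is known from recruitment. What remains is that facility is not named in any of the places where the article names its baseline and control variables.

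A third inference would be systematic bias in favour of the tool. Randomization rules that out: the imbalance is as likely to work against the tool as for it, and overall type I error stays near 5%. Even the 1.6 case is small beside its own interval, the 10 v 5 split is a 14% tail event, and with no facility gap there is no distortion.

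Admitting women on either drug is not a defect.

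Finally, the article calls the trial exploratory and concedes that its size limits conclusions about effectiveness. That lowers the stakes. It does not remove them, since inferential models at α = .05 are planned for both primary outcomes.

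**Conclusion.** The point holds as a cheap improvement, not as an error in the plan. At N = 30 a noticeable facility imbalance is likely under unstratified allocation: with equal recruitment, 9 v 6 or worse in 47% of trials and 10 v 5 or worse in 14%. Its effect on the continuation odds ratio at 10 v 5 ranges from none to a factor of about 1.6 in either direction, depending on a facility gap that the documents do not give. The harm is conditional distortion and some lost precision in the single trial that is run. The conclusion rests on equal arms, the assumed facility splits and rates, and allocation that does not already use facility.

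**What to change.** - Randomize 1:1 within facility, using small permuted blocks of varying size.
- Prespecify facility as a binary covariate in the GEE for both primary outcomes, with priority over demographic covariates chosen by baseline tests. The odds ratio is then a within-facility comparison and should be reported as such.
- Recording OAT drug at baseline is optional, because facility and drug nearly coincide.

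The cost is two allocation lists instead of one, a sentence in the analysis text and one degree of freedom. The model is already sparse: under either set of assumed rates at the 10 v 5 split, 6.75 of 30 women are expected to discontinue (2.75 + 4, or 3 + 3.75). That is why facility should displace a demographic term rather than lengthen the list.

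The Results section places stage 3 in late 2022, so on the article's timeline the change can precede enrolment. If the full protocol already stratifies by facility, only the facility term in the GEE is needed.

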	Perinatal maternal-fetal attachment	Randomized clinical trial		Prenatal maternal-fetal attachment will be measured with the Maternal Antenatal Attachment Scale [35,36], a reliable and validated 19-item measure of maternal-fetal attachment that includes several response formats and assesses 2 dimensions: 1) quality of attachment (11 items) and 2) intensity of preoccupation (8 items). The total scores range from 19 to 95, with higher scores indicating a higher level of attachment to the fetus [35-39]. Maternal-newborn bonding will be measured via MPAS^f^ [40,41]. It consists of 19 items assessing 3 dimensions: *pleasure in interaction with the infant* (5 items), *absence of hostility toward the infant* (5 items), and *quality of mother-infant attachment* (9 items). Response categories range from 2-, 3-, 4-, to 5-point scales, for different items. The total score ranges from 19 to 95, with higher scores indicating higher maternal postpartum attachment to the baby. The MPAS has been found to have an acceptable level of reliability (Cronbach α ranging from .75 to .79; test-retest reliability *r*=0.86; *P*<.001) [37,40,41].	
	Maternal birth experience	Randomized clinical trial		The Birth Satisfaction Scale-Revised, a 10-item, Likert-type birth satisfaction questionnaire that measures experiences of childbearing, stress, quality of care, and women’s attributes, was psychometrically validated in the United States by our research team [42-44]. Its response categories range from 1=strongly disagree to 5=strongly agree, with higher scores indicating higher birth satisfaction.	
	Maternal Depression	Randomized clinical trial		Assess via the PHQ-9^g^, a psychometrically validated 9-item measure used to assess depression in a variety of populations [45-47]. The PHQ-9 asks participants to report on the degree they were bothered by 9 symptoms over the past 2 weeks (ie, “little interest or pleasure in doing things” and “feeling down, depressed, or hopeless”), with response categories ranging from 0=not at all to 3=nearly every day and higher scores indicating greater levels of depression symptomology.	

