	Maternal stress	Randomized clinical trial		PSI^h^ measures parental stress associated with the perception of having a difficult child or a dysfunctional parent-child relationship and consists of 36 items that are rated on a 5-point Likert scale (from 1=strongly agree to 5=strongly disagree), with higher scores indicative of less total stress [48]. PSI has been shown to possess good psychometric properties and has been validated in numerous samples, including high-risk families [49]. It includes parental distress, parent-child dysfunctional interaction, and difficult child subscales, all of which will be considered individually. The child and parent domains can and will be combined to form a total stress scale score.	
	Breastfeeding	Randomized clinical trial		Assessed via several questions “Are you currently breastfeeding? If yes, ‘How often do you breastfeed your baby?’, if no, ‘How long did you breastfeed your baby.’”	
	Frequency of NAS tool use	Randomized clinical trial		Throughout their third trimester and postpartum, we will also send participants a brief weekly web-based survey link asking about the previous week’s frequency of use of the adapted mobile NAS tool and which specific modules participants viewed most, if any, to track weekly frequency of use and preference of modules.	

^a^NAS: neonatal abstinence syndrome.

^b^SUS: Systems Usability Scale.

^c^CSQ-8: 8-item Client Satisfaction Questionnaire.

^d^OAT: opioid agonist therapy.

^e^ASI-Lite: Addiction Severity Index-Lite.

^f^MPAS: Maternal Postpartum Attachment Scale.

^g^PHQ-9: 9-item Patient Health Questionnaire

^h^PSI: Parenting Stress Index short form.

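### Postpartum anxiety is listed as a secondary outcome, but no measure in the stage 3 schedule is assigned to it

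*Protocol article*

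**What the plan says.** Anxiety appears twice as a secondary outcome of the randomised stage. The Abstract's Methods paragraph lists "postpartum depression and anxiety at 4, 8, and 12 weeks postpartum". The Overview of the Methods lists "breastfeeding initiation and duration, birth satisfaction, and postpartum depression and anxiety" and gives the same three time points.

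The article then describes stage 3 measurement in three places: the schedule in Table 1, the outcome-by-outcome descriptions in Table 2, and the stage 3 section on data collection and outcomes.

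- **PHQ-9** (Table 2, maternal depression): "a psychometrically validated 9-item measure used to assess depression in a variety of populations", with "higher scores indicating greater levels of depression symptomology".
- **PSI short form** (Table 2, maternal stress): it "measures parental stress associated with the perception of having a difficult child or a dysfunctional parent-child relationship". On its subscales: "It includes parental distress, parent-child dysfunctional interaction, and difficult child subscales".
- **Birth Satisfaction Scale-Revised** (Table 2, maternal birth experience): a "birth satisfaction questionnaire that measures experiences of childbearing, stress, quality of care" and women's attributes.
- **ASI-Lite** (Table 2): the instrument for maternal drug use and relapse. One of its several domains is psychological.

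None of the three places has a row or sentence for anxiety. Apart from the two outcome lists, the word occurs only in the Background, in a remark on downstream health costs.

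**The concern.** An outcome named with its time points commits the trial to report it. Here the article names the outcome but not the instrument, the score or its direction. The Data Analysis section for stage 3 plans generalized estimating equations for the secondary outcomes, and for anxiety no dependent variable is specified.

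Two things could follow if the surveys run as printed. Anxiety could go unreported although it was prespecified. Or someone could pick a proxy, such as the PSI parental distress subscale or something from the ASI-Lite, once the data are in. The plan proposes no such substitution. If one were made after the data are seen, it would be a post hoc outcome definition, and with several candidate scores and three visits a reader could not tell how the choice was made. A statistical analysis plan could settle how an existing score is used, but it could not supply responses to questions that were never asked.

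**Working it through.** No formula applies. The check is whether each outcome named in the Overview has a measure in Table 1, Table 2 or the stage 3 follow-up text.

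| Outcome named in the Overview | Measure assigned |
|---|---|
| OAT continuation (primary) | Single question |
| Maternal drug relapse (primary) | ASI-Lite |
| Length of newborn hospital stay | Single question |
| Newborn readmission | Single question with follow-on items |
| Maternal-newborn bonding | Maternal Postpartum Attachment Scale |
| Breastfeeding initiation and duration | Several questions |
| Birth satisfaction | Birth Satisfaction Scale-Revised |
| Postpartum depression | PHQ-9 |
| Postpartum anxiety | None |

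Counting depression and anxiety separately, and breastfeeding as one, there are 2 primary + 7 secondary = 9 outcomes. Eight have a measure and 9 − 8 = 1 has none. For that one, the number of follow-up visits with a designated measure is 0 of 3.

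Next, could any scheduled postpartum instrument be read as the anxiety measure?

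1. PHQ-9: the article describes both the construct and the meaning of the score as depression. It mentions no anxiety score.
2. PSI: the construct is stress tied to the child and the parent-child relationship. None of its three named subscales is anxiety, and Table 2 files it under maternal stress.
3. Birth Satisfaction Scale-Revised: it includes stress, but as part of the childbearing experience.
4. ASI-Lite: repeated postpartum and has a psychological domain. Table 2 gives it the task of measuring drug use and relapse, does not say that the domain covers anxiety, and derives no anxiety score from it.
5. The remaining rows of Table 1 cover attachment, satisfaction with the tool, usability, newborn stay, readmission, breastfeeding, OAT status and tool use.

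Finally, the reverse check. Parenting stress is measured by the PSI at all three visits but appears in neither list of secondary outcomes. So the lists and the schedule differ in both directions: anxiety is listed without a measure, and parenting stress is measured without being listed. That fits either an omitted scale or a loose label. The article does not say which.

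**The case against.** Three points can be made on the other side.

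First, a reader might infer that the trial will hold no information related to anxiety and could never report on it. The documents do not support that. The ASI-Lite, with its psychological domain, and the PSI, whose parental distress subscale is to be considered individually, are both collected at 4, 8 and 12 weeks, so some related information may exist. This limits the claim but does not close the gap, because neither instrument is assigned to anxiety and no anxiety score is defined from either. What stands is that no measure is specified.

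Second, a journal article condenses a fuller protocol, so silence can be innocent. That carries little weight here. The article prints a complete-looking measurement schedule and a table of measures by outcome, down to the wording of single questions, and each of the other named outcomes appears in it. The lists and the tables disagree within one document.

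Third, the consequences are limited, and this stands. Anxiety is half of one compound secondary item. Neither primary outcome depends on it, and nothing in the article ties it to sample size, eligibility, randomisation or the analysis of another outcome. The article calls the trial exploratory and means it to inform a fully powered one. A reader might infer that the main comparison is compromised; nothing in the document shows that. Nor does this mismatch require a baseline anxiety measurement: Table 1 schedules the PHQ-9 only postpartum, so consistency with depression needs only the three follow-up visits.

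**Conclusion.** The point holds as an internal inconsistency, and the article is wrong as written. Postpartum anxiety is a stated secondary outcome at three time points, and none of the three accounts of stage 3 measurement assigns it an instrument. As specified, the trial has no designated anxiety data: one of nine named outcomes is uncovered, at 0 of 3 visits.

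It should be fixed but does not threaten the trial, since both primary outcomes and the other six secondary outcomes keep their measures. The conclusion assumes that Tables 1 and 2 show the stage 3 survey content as planned. If the full protocol contains an anxiety scale, the article's tables still need correcting, but no data would be lost. Timing matters because questions omitted at a visit cannot be asked for that visit later. The Results section places stage 3 in late 2022, after the article was written, which left room to correct this before enrolment.

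**What to change.** Before stage 3 begins, the sponsor should state which construct was intended and bring the outcome lists and the schedule into line.

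- **If anxiety was intended:** add a short validated anxiety scale at 4, 8 and 12 weeks to Table 1, Table 2 and the stage 3 follow-up text, naming the score to be analysed and its direction. The cost is a few more items per survey. A 7-item scale, for illustration, would add 7 × 3 = 21 responses per woman, or at most 21 × 30 = 630 over the trial.
- **If anxiety was not intended:** remove it from the secondary outcomes in the Abstract and the Overview. This is one word in two places, with no added burden.
- **If parenting stress was intended:** replace anxiety with parenting stress in both places and name the PSI as its measure. The PSI is already scheduled, so nothing further need be collected.

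The first option keeps the stated outcome at the price of a slightly longer survey. The other two give up a planned comparison on anxiety. Any of them is better made before outcome data are seen.
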